### Secondary outcome measures

*Health-related quality of life* will be measured as a secondary outcome, using the Short Form-36 Health Survey (SF-36). It is a patient-reported and subjective measure of generic health-related quality of life [26, 27]. The SF-36 has eight subscales and two summary measures (physical and mental components), and each scale is transformed to a score from 0 (worse health status) to 100 (best health status). It has been validated [28] in Chile and has been widely used [29, 30].*Clinical outcomes* will be measured using the Outcome Questionnaire (OQ 45.2). It is a self-administered, 45-item instrument that measures psychotherapy outcomes [31, 32], which has been validated in Chile and also widely used [33–35]. It considers three domains: symptoms and distress, interpersonal relationships, and social role.

### Other outcomes

Patients' adherence to treatment and use of health care services will be measured at 3 and 6 months after the baseline assessment. At the primary care team level, the rate of treated depressed cases will be measured 12 months before and after randomization.

### Sample size

Sample size calculation was done based on two studies previously carried out in Chile [36, 15]. A randomized clinical trial that compared pharmacotherapy monitored by telephone with usual care in primary care clinics in Chile found a recovery rate for depressive disorders of 62 % in the intervention group versus 38 % in the control group [36], having an effect size of 20 %. Since the current study protocol aims to test whether the intervention is better than usual care, a one-sided test is appropriate to detect an effect. Moreover, it is expected that the intervention will have a favorable effect ruling out the possibility of a statistically significant negative effect. To detect a difference of 20 %, in a one-sided model, with an alpha of 5 % and power of 80 %, 152 depressed persons, 76 in each group (intervention and control), will be required for the study. Using a database from another study comprising 201 persons treated for depression in seven primary care clinics [15], an intraclass correlation coefficient (ICC) of 0.03839 was estimated. Therefore, a design effect of 2.42 was determined, based on the previously calculated ICC and the use of four clusters (primary care clinics). After applying the design effect, the sample needed increased to 368 depressed persons. Considering a retention rate of approximately 85 %, 434 depressed cases will be required for the study, hence 109 cases in each of the four primary health care clinics.

Finally, a group of four primary health care clinics was chosen for two reasons: the usual flow of patients with depression presenting at each of the participating primary care clinics, which allows for a high number of potential participants per clinic, and financial constraints restricted the number of clusters, since having more primary care clinics would put in jeopardy the feasibility of the study.

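### The design effect of 2.42 is computed at 38 patients per clinic but 92 will be analysed in each, so the stated 80 % power is not delivered and four clinics cannot reach it at the plan's own ICC

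*Protocol article*

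**What the plan says.** All of the following is in the protocol article, Sample size.

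- The calculation is made "in a one-sided model, with an alpha of 5 % and power of 80" per cent, for a difference of 20 % between arms. The motivating trial is reported as "62 % in the intervention group versus 38 % in the control group", and the text labels this an effect size of 20 %.
- Before clustering: "152 depressed persons, 76 in each group (intervention and control), will be required for the study".
- From 201 persons in seven clinics, "an intraclass correlation coefficient (ICC) of 0.03839 was estimated".
- From this, "a design effect of 2.42 was determined, based on the previously calculated ICC and the use of four clusters". The cluster size used is not given.
- "After applying the design effect, the sample needed increased to 368 depressed persons". Allowing for about 85 % retention, the total becomes 434, "hence 109 cases in each of the four primary health care clinics".
- Four clinics were chosen because of patient flow and funding. The section does not say that this costs power.

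The Group assignment section adds that two municipalities each contribute one intervention clinic and one control clinic, so there are two clinics per arm.

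**The concern.** The usual design effect, 1 + (m − 1) × ICC, depends on m, the number of patients analysed per cluster. When the number of clusters is fixed, inflating the sample raises m, and that raises the design effect again. A single inflation at the starting cluster size therefore falls short, and with few clusters the target may be out of reach altogether. The section shows no second step, and 2.42 looks too small for clinics that each supply about 92 analysed patients.

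If so, the trial is described as having 80 % power when its own inputs say otherwise. A non-significant result could then be read as evidence of no effect, and reaching 434 would be thought to secure a precision that it does not.

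**Working it through.** **Inputs** (protocol article, Sample size): one-sided alpha 5 %, power 80 %, difference 20 points, 152 patients before clustering, ICC 0.03839, four clinics, 368 analysed, 434 recruited. The pair of rates behind the 20 points is not stated. I assume 38 % versus 58 %; 40 % versus 60 % gives the same answers to within a tenth of a point or so.

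**1. The plan's own chain**

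- Patients per arm, pooled-variance formula, 0.38 versus 0.58 (mean 0.48):
  n = [1.645 × √(2 × 0.48 × 0.52) + 0.842 × √(0.2356 + 0.2436)]² / 0.20² = 76.1. The plan has 76.
- Cluster size implied by 2.42: m = 1 + (2.42 − 1)/0.03839 = 37.99, i.e. 38 = 152/4. Check: 1 + 37 × 0.03839 = 2.4204.
- 152 × 2.42 = 367.8, giving 368. 368/0.85 = 432.9, close to the stated 434; 434/4 = 108.5, giving 109.

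The chain reproduces, but only with the cluster size before inflation.

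**2. Design effect at the planned size**

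- Analysed per clinic: 368/4 = 92.
- Design effect: 1 + 91 × 0.03839 = 4.49.
- Effective sample: 368/4.4935 = 81.9, or 40.95 per arm, against 152 (76 per arm).
- If all 109 per clinic were analysed: design effect 1 + 108 × 0.03839 = 5.15, effective sample 436/5.146 = 84.7.

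**3. Power for 20 points (normal theory, ICC treated as known)**

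- SE = √((0.2356 + 0.2436)/40.95) = 0.108.
- Power = Φ(0.20/0.108 − 1.645) = 0.58. The pooled-variance version gives 0.57.
- Difference detectable with 80 % power: (1.645 + 0.842) × 0.108 = 0.27, about 27 points.

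**4. Ceiling with four clinics**

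- As m grows, 4m/[1 + (m − 1) × ICC] tends to 4/0.03839 = 104.2, which is below 152.
- At 52.1 per arm, power is 0.67 (unpooled) or 0.66 (pooled). No number of patients in four clinics reaches 80 % for 20 points at this ICC.
- For comparison, four clinics per arm with 68 analysed in each would do so under the same approximation: 8 × 68/(1 + 67 × 0.03839) = 544/3.572 = 152.

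**5. Dependence on the ICC** (92 per clinic, 38 % versus 58 %, unpooled)

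| ICC | Design effect | Effective N | Power |
|---|---|---|---|
| 0.0156 | 2.42 | 152 | 81 % |
| 0.02 | 2.82 | 130 | 75 % |
| 0.03839 | 4.49 | 82 | 58 % |
| 0.05 | 5.55 | 66 | 51 % |
| 0.10 | 10.10 | 36 | 34 % |

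The planned 368 matches the plan's requirement only if the ICC is at most 1.42/91 = 0.0156. The planning ICC is itself imprecise: with seven equal clinics of 201/7 = 28.7 patients (an assumption), its approximate 95 % interval runs from 0 to 0.25.

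**6. If clinic variance has to be estimated**

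With a t reference at clinic level and noncentrality 0.20/0.108 = 1.85, power is about 35 % on 2 degrees of freedom (four clinics, two arms) and about 23 % on 1 (two pairs, same ICC).

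**7. The cited effect**

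62 − 38 = 24 points, not 20.

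**The case against.** The strongest points on the other side are these.

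- **Matching.** Clinics are paired within municipality, which may remove part of the between-clinic variance contained in an ICC from seven clinics. Four clinics can supply 152 effective patients in principle once the ICC is below 2/76 = 0.0263. This is a fair limit on the finding, which holds at the plan's own ICC. But the Sample size section takes no credit for pairing and gives no matched ICC, so it does not support 80 %. It does make the 23 % figure, which charges for pairing without crediting any gain, close to a worst case.
- **The t-based powers assume a clinic-level test.** The article does not specify one; Data analysis names only multivariable linear regression. That stands, so 35 % and 23 % are conditional and the main figure is the normal-theory 57–58 %. The two standards should not be mixed: at ICC 0.0156 the t-based powers are only about 51 % and 31 %.
- **The primary analysis compares mean PHQ-9 scores.** Power for that analysis cannot be derived from the article. True, but the stated 80 % refers to the 20-point binary difference, and that is the claim being checked.
- **The observed effect was 24 points, so planning on 20 is cautious.** At 24 points (38 % versus 62 %), power with 92 per clinic is still only 71–72 %, and even unlimited recruitment brings it to about 80–81 %.
- **Four clinics were a disclosed feasibility choice.** That explains the number of clusters; it does not make the power statement correct.

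Nor is this a detail that a condensed article leaves out. The article gives the whole chain, and the chain disagrees with its own clinic size.

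**Conclusion.** The concern holds and must be fixed. The design effect belongs to clinics of 38, while the same paragraph plans clinics of 92 analysed. At the stated ICC the correct value is 4.49 rather than 2.42, the effective sample is 82 rather than 152, and power for the 20-point binary target is about 57–58 % rather than 80 %, with a ceiling of about 66–67 % for any recruitment into four clinics. The mislabelled cited effect (24 points, called 20) is a separate and smaller slip.

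The design effect and the ceiling on the effective sample rest only on the document's figures and equal clinic sizes. The power figures also assume rates near 38 % and 58 %, normal theory with a known ICC, and no gain from matching. The first hardly matters, and the second is generous to the plan. A gain from matching could raise power, but the documents do not quantify it.

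**What to change.** Keep the four clinics and 434 patients, and rewrite the Sample size section as follows:

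1. Give the design effect as 4.49 at 92 analysed per clinic, and the effective sample as about 82.
2. Replace the 80 % claim with power of about 58 % for 20 points at ICC 0.03839, with about 75 % at ICC 0.02 and 34 % at ICC 0.10. State that these figures refer to the binary remission target under normal theory and do not include the further loss from having only four clinics.
3. Give the detectable difference at 80 % power as about 27 points on the same basis.
4. State that more patients in four clinics cannot bring power to 80 % at this ICC.
5. Correct the cited effect to 24 points, and state which pair of rates underlies the 20-point target.
6. Present the trial as estimating the effect with a confidence interval, not as an 80 %-powered test, so that a non-significant result is not read as absence of effect.

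This costs rewording and a less favourable power statement. It needs no additional patients, clinics or procedures.

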### Recruitment

After being informed of the study by primary health care professionals, interested potential participants with possible cases of depression identified in routine clinical practice will be invited for an on-site or telephone evaluation by a study psychologist, who will obtain participants' informed consent, carry out a baseline evaluation and determine whether or not a potential participants fit study criteria.

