## Methods and design

This is a two-arm, single-blind (blinded only to outcome evaluator), cluster randomized controlled trial, which will compare the effectiveness of a comprehensive technology-assisted training and supervision program for depression management versus usual depression care in primary care clinics in Santiago, Chile.

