### Hypotheses

Adults receiving the intervention will reach clinical remission, given by a score of 10 or less in the PHQ-9, with a difference of 20 % when compared with the group receiving the usual care, 3 and 6 months after randomization.Adults participating in the intervention program will have (significantly) better adherence to treatment than those receiving usual care, 3 and 6 months after randomization.Adults participating in the intervention program will have significantly better quality of life than those receiving usual care, 3 and 6 months after randomization.Adults participating in the intervention program will have significantly better clinical outcomes than those receiving usual care, 3 and 6 months after randomization.Adults participating in the intervention program will have significantly greater service use than those receiving usual care, 3 and 6 months after randomization.Primary care teams participating in the intervention program will treat more depressed cases than those that are only in the usual care program, during a 1-year timeframe.

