### Intervention arm

The intervention arm includes a 16-h training program for primary care teams (physicians, psychologists, social workers, nurses, midwives, and occupational therapists) to ensure compliance with the Clinical Guidelines for the Treatment of Depression, issued by the Chilean Ministry of Health [10]. The workshop will include a seminar on the detection, diagnosis, and treatment of depression; discussion of clinical cases; and role-playing to enhance clinical skills and to apply problem-solving techniques. Finally, trained primary care teams will undergo an Objective Structured Clinical Examination (OSCE) for evaluation.

After the training, a focus group between primary health care teams and study researchers will be held in order to address barriers to the implementation of clinical guidelines. In order to develop a comprehensive supervision program, trained administrative staff will contact patients from a call center to support treatment adherence, and a psychiatrists will supervise the primary care team, using a web-based platform.

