### Control arm

The control arm will receive treatment as usual − all the interventions that are guaranteed for persons with depression from the primary care clinics and if needed referral to the specialized psychiatric service, as indicated by the national depression program. Professionals will be told to follow the Clinical Guidelines for the Treatment of Depression [10].

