### Group assignment

Clustered treatment assignment will be performed. First, two urban municipalities of the Metropolitan Region of Santiago, Chile, which collaborate with the Faculty of Medicine of Universidad de Chile and have at least two primary health care clinics, will be randomly selected through simple random sampling. Municipalities with a high Human Development Index, a high percentage of immigrants and older population, and psychiatry residents working in primary health care clinics will be excluded. In each selected municipality, the two primary health care clinics with the highest registered number of patients will be randomly assigned to the active or the control arm, through simple random sampling, thus selecting a total of four primary health care centers, one from the intervention arm and one from the control arm, in each selected municipality. This matching was done in order to ensure similarity between the patients’ socioeconomic levels and the administration and organization of the primary care centers, since all centers within a municipality are overseen by the same administration.

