### Data collection

All participants will be assessed at baseline and at 3 and 6 months after recruitment. Independent interviewers blind to treatment assignment evaluated participants at 3 and 6 months after baseline assessment. The interviewers received an 8-h training to ensure standardization of data collection, which will be performed using digital PDF forms. Interviewers and patients will use computer tablets for data entry.

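### Unblinded clinic staff, trained in detection in one arm only, identify participants after clinics are allocated, so case mix can be expected to differ by arm, and baseline adjustment is only conditional

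*Protocol article*

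**What the plan says.** All references are to the protocol article.

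- **Allocation and blinding.** Whole clinics are allocated. In each municipality, "the two primary health care clinics with the highest registered number of patients will be randomly assigned to the active or the control arm" (Group assignment). The design is a "two-arm, single-blind (blinded only to outcome evaluator), cluster randomized controlled trial" (Methods and design). For data collection the article states: "Independent interviewers blind to treatment assignment evaluated participants at 3 and 6 months after baseline assessment" (Data collection). Nothing similar is said about the baseline assessment.
- **Training.** In the intervention arm, "The workshop will include a seminar on the detection, diagnosis, and treatment of depression" (Intervention arm). For the control arm the article says only: "Professionals will be told to follow the Clinical Guidelines for the Treatment of Depression" (Control arm).
- **Entry route.** Clinic professionals tell patients about the study, and "interested potential participants with possible cases of depression identified in routine clinical practice will be invited for an on-site or telephone evaluation". A study psychologist takes consent, does the baseline evaluation and decides eligibility (Recruitment). Depression is assessed with the PHQ-9 and the MINI, and no PHQ-9 threshold for entry is given (Inclusion and exclusion criteria).
- **Expected effect on case numbers.** The last hypothesis is that "Primary care teams participating in the intervention program will treat more depressed cases than those that are only in the usual care program" (Hypotheses).
- **Analysis.** Mean symptom scores are compared by multivariable linear regression. Baseline outcome variables enter the model only when an imbalance is detected (Data analysis).

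**The concern.** Randomising clinics balances, in expectation, the populations the clinics serve. It does not protect the sample when patients are identified after allocation by people who know the allocation. Here the intervention also acts on the step that creates the sample, because teams in one arm are taught to detect and diagnose depression and those teams then supply the candidates.

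If trained teams bring in patients with a better prognosis, the intervention arm will look better at 3 and 6 months without any treatment effect. If they bring in harder cases, a real effect will be hidden. Enrolling more patients does not reduce a bias of this kind, and two clinics per arm leave little scope for chance to even out case mix.

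The analysis offers one direct protection, adjustment for the baseline score, but makes it depend on an unspecified finding of imbalance.

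**Working it through.** The article gives no figure for this point. The planned total of 434 is not in dispute here. The check is whether each link in the mechanism is supported, followed by an illustration of size.

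**1. Do the staff who identify patients know the allocation?** Yes. Blinding is limited to the outcome evaluator, and the teams either attend the training or do not.

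**2. Does the intervention change identification?** It is meant to. Detection and diagnosis are part of the workshop, and more treated cases are predicted in that arm. The Background adds that an evaluation at seven Chilean clinics found severity inaccurately diagnosed and underestimated, so training that works would plausibly change who is recognised.

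**3. Does recruitment follow allocation?** This is not stated outright, but it follows from the dates. Recruitment runs from June 2014 to July 2015 (Trial status), and each patient is assessed 3 and 6 months after recruitment (Data collection). June 2014 plus 6 months is December 2014, about seven months before recruitment closes. Had allocation and training waited for full enrolment, the first patients would have finished follow-up before the intervention began. The article also counts follow-up from randomisation in Hypotheses and Data analysis, but from baseline or recruitment in Other outcomes and Data collection. These should be reconciled, since a clinic is randomised once while its patients enter over about a year.

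**4. What do the safeguards cover?**

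| Safeguard | What it limits | What it leaves |
|---|---|---|
| PHQ-9 and MINI by a study psychologist | Entry of people who are not depressed | Severity, motivation and prognosis among eligible patients |
| Pairing within municipality | Socioeconomic and administrative differences | Who is identified and informed within a clinic |
| Adjustment when imbalance is found | Measured baseline differences, if triggered | Gaps that do not trigger it, and unmeasured selection |

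**5. Illustration of an unadjusted comparison.** Assumptions, not in the article: mean baseline PHQ-9 differs by 1 to 2 points, and the slope of follow-up on baseline score is 0.4 to 0.6.

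Bias = baseline gap × slope

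- Low end: 1 × 0.4 = 0.4 points
- High end: 2 × 0.6 = 1.2 points

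**6. Would the conditional rule catch such gaps?** Assume a baseline SD of 6 (not in the article) and 434 / 2 = 217 per arm.

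- Ignoring clustering, SE = 6 × √(2/217) = 0.58. A 1-point gap is 1 / 0.576 = 1.7 SE and a 2-point gap is 2 / 0.576 = 3.5 SE.
- With the article's design effect of 2.42, SE = 0.576 × √2.42 = 0.90. The same gaps are 1 / 0.896 = 1.1 and 2 / 0.896 = 2.2 SE.

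A 2-point gap would probably be noticed. A 1-point gap might well not be, which would leave 1 × 0.4 = 0.4 to 1 × 0.6 = 0.6 points of bias in the estimate. The article does not say what counts as an imbalance, so the outcome cannot be settled further.

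**The case against.** Several stronger readings are tempting, and the article does not support them.

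- **That the arms will certainly differ, or that the intervention arm will enrol milder cases.** The hypothesis concerns the number of cases treated, not their severity. Neither direction nor size is fixed.
- **That clinic staff choose the sample.** They identify and inform. Patients must be interested, and a study psychologist decides eligibility with criteria that are not arm-specific.
- **That the baseline psychologist is unblinded.** The article limits blinding to the outcome evaluator and describes it only for follow-up, so masking at baseline is not stated. A fuller protocol might describe it, and might also describe screening logs.
- **That the bias is 13 to 40 % of the target effect.** This comes from dividing 0.4 to 1.2 by about 3 points, a value that itself needs an assumed SD of 6 and a conversion from a 20-point remission difference. It also describes an unadjusted comparison, whereas the plan adjusts when imbalance is found, most likely at the upper end of the range. It is not an expected bias.

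Some remedies that come to mind also fall short. Having clinics forward every depression case they register would remove discretion over whom to inform, but registration itself depends on detection. Restricting the analysis to the severity range common to both arms may change little, because ranges can overlap almost fully while means differ. On-site evaluation can reveal allocation, since each clinic belongs wholly to one arm.

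These objections limit certainty, size and choice of remedy. They do not touch the mechanism or the conditional adjustment rule, which the article states explicitly.

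**Conclusion.** The point holds as an expected risk of differential recruitment, not as a demonstrated imbalance. Unblinded staff, detection training in one arm only and identification by those same teams are stated. Recruitment after allocation is inferred from the dates. The common eligibility check and municipal pairing reduce the risk without removing it.

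The size is unknown. The range of 0.4 to 1.2 PHQ-9 points applies only to an analysis left unadjusted and only under the assumed gap and slope. Once baseline PHQ-9 is adjusted for, what remains is unmeasured selection, for which the article gives no basis for a figure. The clearest defect in the plan as written is that adjustment for a score already collected on every participant depends on an undefined trigger.

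**What to change.** **Analysis (applies to all patients, including those already enrolled).** In Data analysis, replace the conditional rule with adjustment for baseline PHQ-9 in every primary analysis, and for the matching baseline score in each secondary outcome analysis. The data are already collected, so this costs nothing.

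**Remaining recruitment.**

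1. Keep the baseline psychologist unaware of clinic allocation where feasible, for example in telephone evaluations.
2. State one PHQ-9/MINI entry rule and apply it in all four clinics.
3. Record and report, per clinic, the numbers informed, evaluated, eligible and consenting, together with baseline severity.

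**Reporting.** State that adjustment cannot remove unmeasured selection, and that conclusions will be qualified if recruitment rates or case mix differ by arm. Use one starting point for follow-up throughout.

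The cost is a short amendment and a small logging burden. Patients already enrolled are covered only by the analysis change.
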